## Abstract

**Background:**

Although hippotherapy treatment has been demonstrated to have therapeutic effects on children with cerebral palsy, the samples used in research studies have been very small. In the case of hippotherapy simulators, there are no studies that either recommend or advise against their use in the treatment of children with cerebral palsy. The aim of this randomised clinical study is to analyse the therapeutic effects or the contraindications of the use of a commercial hippotherapy simulator on several important factors relating to children with cerebral palsy such as their motor development, balance control in the sitting posture, hip abduction range of motion and electromyographic activity of adductor musculature.

**Methods/Design:**

The study is a randomised controlled trial. It will be carried out with a sample of 37 children with cerebral palsy divided into two treatment groups. Eligible participants will be randomly allocated to receive either (a) Treatment Group with hippotherapy simulator, maintaining sitting posture, with legs in abduction and rhythmic movement of the simulator or (b) Treatment Group maintaining sitting posture, with legs in abduction and without rhythmic movement of the simulator. Data collection and analysis: all measurements will be carried out by a specially trained blind assessor. To ensure standardization quality of the assessors, an inter-examiner agreement will be worked out at the start of the study. The trial is funded by the Department of Research, Innovation and Development of the Regional Government of Aragon (Official Bulletin of Aragon 23 July 2007), project number PM059/2007.

**Discussion:**

Interest in this project is due to the following factors: Clinical originality (there are no previous studies analysing the effect of simulators on the population group of children with CP, nor any studies using as many variables as this project); Clinical impact (infantile cerebral palsy is a chronic multisystemic condition that affects not only the patient but also the patient's family and their close circle of friends); Practical benefits (the development of an effective treatment is very important for introducing this element into the rehabilitation of these children).

**Trial registration:**

Current Controlled Trials ISRCTN03663478.

## Background

Hippotherapy is a physical treatment strategy in which the movement of a horse is used to improve posture, balance and general development of people with or without motor difficulties. It has been used since the 1960s in Europe and the mid 1970s in the USA for the treatment of cerebral palsy (CP) as well as other neurological pathologies such as multiple sclerosis, traumatic brain injury, learning disabilities, muscular dystrophy and sensorial problems. It is based on current theories of motor control and development, and neurophysiological treatment principles.

Several research studies have been published [1-13] showing the beneficial effects of hippotherapy on patients with disorders of the central nervous system, including infantile CP. Current studies of the beneficial effects of hippotherapy in the treatment of children with CP have a scientific evidence level of 2a [14]. The main studies have been carried out on the basis that the horse's gait provides a precise, rhythmic and repetitive pattern of movement similar to the movements of human walking [15]. Therefore, a patient whose disability has impeded the development of a rhythmic walking pattern can be helped to acquire reciprocal aspects of movement and to improve posture control through the stimulation of normal balance reactions and through repetitive stimuli for posture coordination during the hippotherapy session [16,17].

The therapeutic results obtained with the application of hippotherapy treatments has encouraged research into developing an advanced hippotherapy platform or simulators that "imitate" the movements of a horse, so that this therapy may be more accessible and adaptable to patients.

A detailed study of the work developed in this line of research or associated disciplines enables the following classification to be drawn up of types of equine movement simulators:

Structures of the Karakuri type [18,19] designed to give the sensation of "riding a horse" and "trotting" by means of a combination of forward-backward and up-and-down oscillating movements. It is generally aimed for uses requiring a great sensation of movement rather than fine and precise adjustments [20].

Structures based on hexapods with geometry of parallel platforms, with the upper platform being completely moveable. Hexapods allow a greater degree of moveability and adjustment, ideal for more precise movements at the expense of greater structural complexity.

Technologies with specific mechanisms, such as those developed by Matshushita (Panasonic) or Osim based on the use of eccentric cams and followers (ad-hoc solution).

In any event, the development of mechanical simulation systems for hippotherapy appears to be innovative and not much exploited. There is no diversified work within this research area.

In short, starting from existing studies about the benefits of hippotherapy and taking into account the scarcity of studies carried out with simulators (and none with children with CP) the aim is to develop a study on the effects of the use of a simulator with these children with respect to two actions: remaining in the sitting position (trunk stability) and influence on the hip joint, with the simulator working providing a rhythmic movement imitating a horse walking and with the simulator used simply as a sitting device with no movement.

This study is especially novel for two reasons. First, because the sample of children is substantially greater than that of other published studies concerning traditional hippotherapy, and the study is not limited to less serious cases. Second, because the therapeutic effect of a hippotherapy simulator is to be studied on a population group about whom no published data is available about the use of simulators.

### Objectives

The main objective to be achieved in this project is to study the therapeutic relevance of a hippotherapy simulator for the treatment of children with cerebral palsy (considering four outcome variables, which are: sitting stability, muscle activity in hip adductors, range of hip abduction mobility and global motor development). We will study and divide the effect of the hippotherapy simulator into two aspects:

- Maintenance of a therapeutic stance.

- Rhythmic and repetitive movement produced by the simulator, that is similar to the normal mechanics of the human step.

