**Figure 1 F1:**
[figure not shown]
**Randomised controlled trial design**.

The patients will be classified into five levels according to the Gross Motor Function Classification System (GMFCS) and subsequently randomly divided into two treatment groups.

1.- Treatment Group with hippotherapy simulator switched on.

2.- Treatment Group with hippotherapy simulator switched off (without rhythmic movement).

The randomising will be centralised and generated by computer according to stratified groups to ensure a similar distribution of the possible confounding variables in both groups. The assignation sequence will be concealed.

Ten treatment sessions (one weekly) will be given in each modality, in which the children will do different activities proposed by the physiotherapist according to their motor possibilities.

In the treatment sessions with the hippotherapy simulator switched on, the children will maintain the sitting position for 15 minutes on the simulator, with an active extension of the trunk, stabilization of the pelvis and abduction of hips while the simulator produces a rhythmic and repetitive movement that is similar to a walking horse. In the treatment sessions with the simulator switched off (without providing the rhythmic movement), the children will maintain the active extension of the trunk, stabilization of the pelvis and abduction of hips but they won't benefit from the rhythmic effects produced by the hippotherapy simulator. That is, the children who sit on the simulator that is switched off will receive the same treatment except that they won't receive rhythmic movement from the simulator (it would be similar to sitting on a barrel or another device in which they maintain this sitting position, similar to other studies published^7^).

Children not included in the group with the simulator switched on will be offered the possibility to receive ten more treatments with the simulator switched on once the research has concluded.

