### Statistical analysis

The data will be entered and analyzed with SPSS 14.0, and the following statistical procedure will be undertaken:

1. Descriptive analysis of defined variables.

2. Mean comparison tests for quantitative variables and comparison of proportions for qualitative data, among independent variables to check the comparability of the groups.

3. Mean comparison tests for each outcome variable according to the treatment group (differences pre-post treatment in both treatment groups as well as differences between them)

4. Multivariate analysis to determine the influence of independent variables in the evolution of each outcome variable.

A descriptive analysis of drop outs will also be made in order to determine if there are correlating patterns.

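### The objective says the simulator's effect will be divided into stance and movement, but both randomised arms hold the stance, so the comparison identifies only the added effect of movement

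*Protocol article*

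**What the plan says.** The Objectives section sets the main objective as the therapeutic relevance of the simulator on four outcomes and continues: "We will study and divide the effect of the hippotherapy simulator into two aspects". The two aspects are "Maintenance of a therapeutic stance" and "Rhythmic and repetitive movement produced by the simulator, that is similar to the normal mechanics of the human step".

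The design has two arms. Under Study design (text below Figure 1), children are graded by GMFCS level and "subsequently randomly divided into two treatment groups". The Abstract describes the arms as "Treatment Group with hippotherapy simulator, maintaining sitting posture, with legs in abduction and rhythmic movement of the simulator" and "Treatment Group maintaining sitting posture, with legs in abduction and without rhythmic movement of the simulator". The Study design text confirms that "the children who sit on the simulator that is switched off will receive the same treatment except that they" do not receive the movement. In both arms the child sits with active trunk extension, a stabilised pelvis and abducted hips.

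Under Study variables, all four outcomes are measured at the start, after ten weekly sessions and after a 3-month follow-up. Hip abduction range and adductor EMG are also measured before and after each session. No untreated run-in is described. Switched-on sessions are offered to the other group only after the research has ended.

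Step 3 of the Statistical analysis section plans mean comparison tests of "differences pre-post treatment in both treatment groups as well as differences between them".

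**The concern.** Dividing an effect into two parts requires data that can tell the parts apart. Here the stance is the same in both arms, so randomisation gives no information about it. The only planned analyses that could seem to address it are the within-arm comparisons.

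Two wrong conclusions are then possible. A pre-post gain in the switched-off arm, or in both arms, could be reported as a benefit of the stance although it may reflect growth, other care, familiarity with the tests or regression to the mean. Separately, a significant change in one arm and a non-significant change in the other could be read as evidence for movement. The first follows from the mismatch between objective and design. The second is an additional risk of interpretation.

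**Working it through.** **1. Inputs from the article.** Two arms (Abstract; Study design). Stance in both arms, movement in one (Study design). 17 per group from the power calculation, and at least 18 per group hoped for (Sample). 37 eligible children (Sample).

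**2. The plan's own figure.** The article gives no figure for the stance effect. Its sample size concerns the between-group comparison, 60% against 10% improvement at power 0.90. Alpha is not stated, so I assume two-sided 0.05, pooled variance and no continuity correction. The mean proportion is 0.35:

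n = [1.960 × √(2 × 0.35 × 0.65) + 1.282 × √(0.6 × 0.4 + 0.1 × 0.9)]² / 0.5² = (1.322 + 0.736)² / 0.25 ≈ 16.9, hence 17 per group.

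This agrees with the article. The point below does not depend on it.

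**3. What the arms identify.** Write the mean change in an arm as the sum of T (time, concurrent care, repeat testing, regression to the mean), S (stance) and M (movement added to the stance).

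| Arm | Mean change |
|---|---|
| Switched on | T + S + M |
| Switched off | T + S |

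- On minus off = M. Movement is estimable.
- S = off change − T. T is not observed, so S is not estimable.
- S + M = on change − T. This is not estimable either.

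The design matrix with rows (1,1,1) and (1,1,0) has rank 2 for three components. Adding a row (1,0,0), an arm without the device, raises the rank to 3 and makes all three estimable. For scale only, three arms of 17 would be 51 children, or 57 after 10% drop-out (51 / 0.9 = 56.7), against 37 available.

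**4. Measurements around each session.** For hip abduction range and adductor EMG the same equations apply over a 15-minute session. Growth and school therapy then contribute very little to T, but warm-up and repeated measurement remain. These data also describe the immediate change, not the change over the ten-week course, and cover two of the four outcomes.

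**5. Size of the risk of a false stance finding.** Assume S = 0 and a drift T of d standard deviations of the change score, with n = 18 in the switched-off arm and a two-sided paired t-test at 0.05. The probability of significance comes from the noncentral t distribution with 17 degrees of freedom and noncentrality d√18. The article gives no basis for d, so a range is shown.

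| d (assumed) | Probability of a significant pre-post change |
|---|---|
| 0 | 5% |
| 0.2 | 13% |
| 0.3 | 22% |
| 0.5 | 52% |
| 0.8 | 89% |

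**6. A separate illustration: comparing p-values between arms.** Assume both arms change equally by d, with n = 17 each, so M = 0. With power p in each arm, exactly one arm is significant with probability 2p(1 − p).

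| d (assumed) | p | 2p(1 − p) |
|---|---|---|
| 0.3 | 0.214 | 0.34 |
| 0.5 | 0.491 | 0.50 |
| 0.7 | 0.773 | 0.35 |

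This shows why separate within-arm p-values must not replace the between-group comparison. It does not measure the estimability problem in step 3.

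**The case against.** The strongest reply is that the objective is loosely worded and the design is sound. The Background states the aim in operational terms, as the simulator moving against the simulator used only as a seat, and the Study design section openly likens the switched-off condition to sitting on a barrel. On that reading the trial compares movement with an active comparator, which it does properly. Step 3 plans the between-group comparison. The article also records and monitors concurrent treatments and physical activity, and step 4 models their influence on each outcome. For two outcomes the measurements around each session largely avoid growth and school therapy.

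Much of this stands. The movement comparison is valid and matches the Background. A reader might infer that the trial also promises an effect of the whole simulator against no treatment, but no passage says so. A reader might also infer that the investigators will judge movement by comparing within-arm p-values. The article does not say that either, and plans the direct comparison. Replacing within-group tests by confidence intervals would be largely a reporting preference, and I do not press it.

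What does not stand is that this removes the mismatch. The Objectives section lists the stance as one of two aspects into which the effect will be divided, and the arms cannot do that. Step 4 can adjust for measured differences between children but cannot remove a time trend that all of them share. The session measurements have no control without the stance. Nor is this a detail that an analysis plan could supply, because the objective and the arms are both fixed in the article.

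**Conclusion.** The point holds in a limited form. One of the two aspects named in the main objective, the stance, cannot be separated by this design. The other, the added effect of movement, can. The first conclusion is algebraic and does not depend on sample size, outcome or method of analysis. It assumes only that time and concurrent care may change the outcomes, which is plausible over ten weekly sessions in children aged 4 to 18.

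The size of any error cannot be derived from the article. Under assumed drifts of 0.2 to 0.8 SD and no stance effect, a pre-post test in 18 children would be significant with probability 13% to 89%. These figures, and those for exactly one arm being significant, are illustrations.

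It would go too far to conclude that the trial fails its purpose or that its randomised comparison is compromised. The fault lies in what the objective claims and in what the within-arm results may be used to support.

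**What to change.** 1. Restate the main objective, for example: *to estimate the added effect of the simulator's rhythmic movement over the same sitting position on the switched-off simulator, by the between-group difference in change for each of the four outcomes.*
2. Remove the statement that the simulator's effect will be divided into stance and movement.
3. In step 3 of the Statistical analysis section, make the between-group difference in change the basis for any conclusion. Label the within-group pre-post results as descriptive, supporting no conclusion about stance or about movement. Apply the same label to within-arm changes around each session.

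The cost is a narrower claim and edits to two sections. Arms, sample size, allocation and measurements stay as they are. Estimating the stance effect would need a concurrent group without the stance, which the 37 available children would not support at 17 per arm.

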## Methods

This study has been approved (reference number CP04/06/08) by a Spanish Regional Ethics Committee (CEICA) and consequently the study will be carried out in compliance with the Helsinki Declaration of Human Rights.

Informed consent will be obtained from children's parents or tutors prior to participating in the study.

### Sample

The subjects of the study are children between 4 and 18 years old with CP, who attend schools run by the Education Department of the Government of Aragon (Spain) and whose tutors have signed an informed consent form.

Regarding the sample size, a calculation of statistical power was made previous to the study. The calculation of statistical power was based on a non-published introductory research of the effects of a commercialized hippotherapy simulator for cerebral palsy children. In this study, an improvement of 60% was obtained in cases against 10% of improvement in controls, so improvement probability is considered to be at least double in cases than in controls (odd ratio of 2). In order to assure a power of 0.90 the sample should be 17 in every group (total sample 34). The sample size was considered to be 10% greater due to possible drop-outs (37-38 children).

All CP children that fit the inclusion criteria were selected to participate (37 children). In this study it is hoped to assign at least 18 subjects randomly to each experimental condition.

In cases where tutors or children do not wish to participate, the following variables will be recorded: Sex, age, level of Gross Motor Function Classification System and cause to refuse to participate.

The exclusion criteria are as follows:

- Children who have undergone selective dorsal rhizotomy

- Acute convulsions not controlled by medication

- Allergy to electrode adhesives

- Visual impairment not corrected with glasses

- Those circumstances or associated illnesses that in the judgment of the researcher might interfere with the results or be detrimental to the children.

- Inability to attend intervention sessions or refusal to participate.

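### The sample-size paragraph equates 60% versus 10% improvement with an odds ratio of 2; those rates give 13.5, and 17 per group has about 0.1 power, not 0.90, for a doubling from 10%

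*Protocol article*

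**What the plan says.** The sample-size justification is in the protocol article, Methods, Sample. It rests on an unpublished preliminary study: "In this study, an improvement of 60% was obtained in cases against 10% of improvement in controls". From this it concludes "so improvement probability is considered to be at least double in cases than in controls (odd ratio of 2"). The next sentence gives the size: "In order to assure a power of 0.90 the sample should be 17 in every group (total sample 34"). A drop-out allowance follows: "The sample size was considered to be 10% greater due to possible drop-outs (37-38 children"). The section gives no alpha, sidedness or test for the calculation, and 10% is the only control rate it mentions.

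**The concern.** Three descriptions of the effect are run together: 60% versus 10%, a probability at least doubled, and an odds ratio of 2. Only the first two are compatible, and the second only as a loose lower bound. The power statement comes straight after the odds ratio of 2, so the natural reading is that the pilot result was scaled back to a cautious design effect and that 17 per group gives 0.90 power for it.

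If 17 per group in fact depends on the full 50-point pilot difference, the trial is presented as far more sensitive than it is. A non-significant result could then be taken as good evidence against a doubling of improvement when it says very little about one. Readers cannot check the pilot, because it is unpublished, so they depend on the effect size the paragraph states.

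**Working it through.** **Inputs.** From the Sample section: 60% and 10% improvement, power 0.90, 17 per group, 10% for drop-outs. Assumed, because not stated: two-sided alpha of 0.05 and a comparison of two proportions.

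**1. Effect sizes.**
- 60% versus 10%: odds ratio (0.6/0.4)/(0.1/0.9) = 1.5/0.111 = 13.5; risk ratio 0.6/0.1 = 6.
- Doubled probability from 10%: 20% versus 10%; odds ratio (0.2/0.8)/(0.1/0.9) = 2.25.
- Odds ratio 2 from 10%: odds 2 × (1/9) = 2/9, so probability 2/11 = 18.2% versus 10%.

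**2. Reproducing the plan's 17.** The pooled-variance formula without continuity correction, where p̄ is the mean of the two rates, is

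n per group = [1.96·√(2p̄(1−p̄)) + 1.2816·√(p₁(1−p₁) + p₂(1−p₂))]² / (p₁−p₂)²

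For 60% versus 10%, p̄ = 0.35:

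(1.322 + 0.736)² / 0.25 = 16.9, rounded up to 17.

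This matches the plan and supports the assumed alpha. The drop-out step also reproduces: 34 × 1.1 = 37.4 and 34/0.9 = 37.8.

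**3. The same formula for the effects as worded.**
- 20% versus 10%: (0.990 + 0.641)² / 0.01 = 265.9, so 266 per group.
- 18.2% versus 10%: (0.964 + 0.626)² / 0.0818² = 377.9, so 378 per group.
- Odds ratio 2 at about the most favourable control rate (58.6% versus 41.4%): 177 per group.

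**4. Power at 17 per group, two-sided 5%.** The exact columns sum the binomial probabilities of all tables that the test rejects.

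| Effect | Normal approximation | Exact, uncorrected chi-square | Exact, Fisher |
|---|---|---|---|
| 60% v 10% (odds ratio 13.5) | 0.901 | 0.905 | 0.83 |
| 20% v 10% (doubled probability) | 0.124 | 0.114 | 0.054 |
| 18.2% v 10% (odds ratio 2) | 0.100 | 0.091 | 0.039 |
| 58.6% v 41.4% (odds ratio 2, best case) | 0.165 | 0.187 | 0.105 |

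**5. Sensitivity (normal approximation).**
- One-sided 5%: power is 0.20 for 20% versus 10% and 0.17 for an odds ratio of 2 from 10%.
- Doubling from a higher control rate, two-sided: 0.42 for 30% to 60% and 0.83 for 45% to 90%. No control rate tried, from 5% to 45%, reaches 0.90.
- One-sided, the extreme case of 45% to 90% just reaches 0.906.

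**The case against.** The best defence is that the sample size itself is correct. The section says the calculation was based on the pilot, and 17 per group follows exactly from the pilot rates. The error may be no more than a wrong label in a parenthesis. A six-fold ratio is, literally, at least double, and the power sentence names no effect size, so linking it to the odds ratio of 2 is a reading and not a quotation. Power for a doubling also depends on the control rate and is much better than 0.1 when that rate is high. Finally, the Statistical analysis section plans mean comparisons of the outcomes, so no listed test would directly produce a null result on the proportion improved.

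Much of this is fair. The figure of 17 is not an arithmetic error, and at least double is not false in itself. The figure of about 0.1 applies to a 10% control rate, and the harm from misreading a null result is a risk and not a certainty.

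The central point remains. The odds ratio of 2 is wrong for the rates beside it. It is the last effect size given before the power claim, and 10% is the only control rate in the document. For an odds ratio of 2, no control rate lifts two-sided power above 0.20.

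**Conclusion.** The paragraph is wrong as written. The pilot rates correspond to an odds ratio of 13.5, not 2, and the claimed 0.90 power belongs to 60% versus 10% alone. For the effect as worded, at a 10% control rate, power with 17 per group is 0.09 (odds ratio 2) to 0.11 (doubled probability) by uncorrected chi-square, and lower by Fisher's test. Sizes for 0.90 power would be 378 and 266 per group.

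This rests on an assumed two-sided alpha of 0.05, which the exact match to 17 supports; a one-sided 5% test does not change the conclusion at a 10% control rate. Even for 60% versus 10%, the 0.90 depends on the test, since Fisher's exact test gives 0.83. As this is the only justification of sample size in the article, it needs correcting.

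**What to change.** Rewrite the sample-size paragraph as follows.

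- Remove the odds ratio of 2 and the phrase about at least doubling, which suggests a smaller design effect than the one used.
- Name the powered effect: 60% versus 10% improvement, a difference of 50 points, risk ratio 6, odds ratio 13.5.
- Have the sponsor confirm and state the alpha, sidedness and test. If they were two-sided 5% and an uncorrected chi-square test, say that 17 per group gives about 0.90 power for that effect only.
- State that power for an increase from 10% to 20% is about 0.11, and that a null result will not be read as excluding a doubling.

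Re-sizing for an odds ratio of 2 is not realistic: all 37 eligible children have already been selected, against 378 per group needed from a 10% control rate. The cost is one paragraph and a less favourable statement of power for modest effects. Sample size, allocation and analysis do not change.
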